## Abstract

**Background:**

Russia’s full-scale invasion of Ukraine has deepened the strain on an already fragile mental health system, long shaped by Soviet institutionalized psychiatry. In response, Ukraine has started a national reform to modernize mental health services by shifting from an institutional to a community-based mental health care model. Implementation of his transition is supported by the international technical project Mental Health for Ukraine (MH4U).

**Aims:**

To generate evidence-based evaluation of the community-based mental health centers as a basis for continued improvement and to guide national scale-up.

**Methods and analysis:**

We will conduct a mixed-methods evaluation guided by the RE-AIM framework. First, quantitative data will be collected through (a) questionnaires administered to patient’s prospective longitudinal cohort at baseline, three, and six months, (b) questionnaires from providers at the baseline and in the follow-up, and (c) administrative records. Second, qualitative data will be gathered through (a) interviews with subsample of participating patients and all the providers, and (b) focus groups with community stakeholders for each oblast (administrative region). Analyses will follow the RE-AIM framework. Adhering to a learning health systems (LHS) framework, we established continuous feedback loops and workshops to communicate study findings to MH4U implementers and stakeholders in Ukraine and Switzerland.

**Conclusion:**

Evaluation will provide unique evidence on not only whether the community-based Mental Health Center model works, but also how and why it works in real-world conditions. Findings will also inform national policy on mental health reform and offer lessons for global mental health systems operating under crisis conditions.

**Clinical trial registration:**

https://www.isrctn.com/ISRCTN61471084, ISRCTN61471084.

## Background

The ongoing war in Ukraine is expected to affect the mental health of Ukrainian citizens for decades (1). Ukraine estimated population is 39 million in 2025 (2). In 2023, the World Health Organisation estimates that approximately 9.6 million people in Ukraine are at risk of, or living with, a mental health condition, and 3.9 million with moderate to severe symptoms (3). Furthermore, the Ukrainian Ministry of Health predicts that 4 million people will need psychotropic medication, and up to 15 million will need psychosocial support (4).

Ukraine inherited an institutionalized mental health care system shaped by the Soviet legacy (5). This history has contributed to enduring mistrust and strong stigma surrounding mental health care (6, 7). Nevertheless, the Ukrainian health system long struggled with the lack of clear support pathways for individuals with mental health problems, resulting in delayed access to adequate diagnosis and treatment (5, 8). Social services for people with mental disorders in the community are limited or even absent (9).

Recognizing this historic context, in 2017, the Cabinet of Ministers of Ukraine approved a key strategic document for the reform of the mental health care system: “The Concept Note on Mental Health Care Development in Ukraine”. The Concept Note mandated state-sponsored and international initiatives to modernize and decentralize mental health care in Ukraine (10). A central element of this reform is the transition away from institutionalized social care facilities (internats) toward the community-based Mental Health Center (MHC) model to allow people to receive care while remaining active in their communities (11). MHCs have been shown globally to be an evidence-based model to improve access to care, health, and social inclusion while reducing stigma (12–14). Thus, the Ukrainian government commits to establishing MHCs across the country. MHC provides specialized mental health care alongside non-medicalized psychosocial support for victims of the war and the wider community (15).

International collaborative initiatives have been established to advance the transition to MHCs in Ukraine (16). One key initiative, the Mental Health for Ukraine Project (MH4U) was launched before the 2022 invasion in collaboration with the Ukrainian Catholic University’s Institute of Mental Health and supported by the Swiss Agency for Development and Cooperation (DEZA) (16, 17). MH4U embodies the approaches outlined in the “Concept for the Development of Mental Health Care in Ukraine until 2030.” The concept aims to create a comprehensive and effective mental health care system (8, 18). MH4U provides MHCs with financial support, infrastructure development, training, and implementation guidance in alignment with Ukraine’s national mental health reform (15, 16).

MHCs serve three complementary roles. First, they provide direct mental health services in outpatient and day-clinic settings. Services are delivered by interdisciplinary teams of providers, i.e., psychiatrists, psychologists, psychotherapists, nurses, and social workers. Second, they act as a community hub for care coordination, managing referrals, and collaboration between medical and social service providers who work in alignment with the community to reduce stigma and improve mental health literacy. Third, they engage communities through public awareness, low-threshold prevention, and education initiatives (16).

Despite the potential of MHCs, no studies have evaluated how these MHCs operate in real-world conditions, their capacity to develop and expand, or their integration into communities, especially during wartime. Achieving the full potential of this model requires continuous learning, coordination, and improvement across all levels of the mental health care system.

### Aims

We aim to establish an evidence-based evaluation of the MHC model to guide its refinement and national scale-up in Ukraine.

Measure the real-world implementation and identify potential improvement variables across three levels: community, provider, and patient.Examine how collaboration across the multi-level system affects outcomes.Deliver iterative feedback to stakeholders to support continuous quality improvement and inform policy decisions for the expansion of MHCs.

## Methods and analysis

### Design

We employ a mixed-methods evaluation design guided by the RE-AIM (Reach, Effectiveness, Adoption, Implementation, and Maintenance) framework (19, 20). This framework allows assessment at both individual and organizational levels while capturing both internal and external validity, making it well-suited for evaluating real-world interventions and guiding scale-up efforts (19). Figure 1 shows the phases, sites, and timelines of the study. Consistent with the Learning Health System (LHS) approach, data generated through the evaluation will be continuously fed back to the MH4U team and stakeholders to inform real-time adaptation and improvement (Figure 2) (21).

**Figure 1 fig1:**
[figure not shown]
Overview of study phases, sites, and timeline. Timeline representing study phases, including participating MHCs across four oblasts, measurement and data collection.

**Figure 2 fig2:**
[figure not shown]
Learning health system framework for the MHCs evaluation. Figure represent the LHS applied to MHCs evaluation to produce evidence. The figure illustrate how interpreted data contributes to iterative cycles of knowledge generation, evidence synthesis, and improvement in MHC.

### Study setting and participants

#### MHCs

We will conduct the study across the current eight MHCs and their respective communities, including four in Lviv, two in Chernivtsi, one in Dnipropetrovsk, and one in Rivne. These oblasts may differ in the mental health impact of the war, providing important contextual variation for the evaluation. Mostly, MHCs are structural components of policlinics, i.e., outpatient services. However, in Dnipro, MHC is a part of the Primary Health Care (PHC) service. While in Rivne, MHC is a hospital department within a cluster hospital, providing a network of medical services to more than one community.

### Participants

#### Patients

##### Intervention cohort

The inclusion criteria are: (a) Adults (≥18 years), (b) have received one to three treatment sessions at one of the participating MHCs, and (c) have provided informed consent. Patients will be excluded if they have only received an emergency session or if a treating psychiatrist determines they have severe cognitive dysfunction or an acute mental health condition that would impair their ability to participate.

##### Sample size calculation

We will recruit a prospective longitudinal cohort via a non-probability sampling technique. Each participating MHC representing a cluster because patient outcomes are expected to be correlated within centers due to shared staff, resources and local community. Approximately 400 patients for the 8 MHCs (targeting ~50 per MHC) will be enrolled in the quantitative assessment. The primary outcome is the change in depressive symptoms measured by the Patient Health Questionnaire-9 (PHQ-9) scale from baseline to follow up 4 (approximately one year) (22).

We estimated the variance of the PHQ-9 change score empirically as:

$$\mathrm{Var}\;(\Delta )=\sigma_{b}^{2}+\sigma_{f}^{2}-2r\sigma_{b}\sigma_{f}\;$$

Where 
$\sigma_{b}=5.97$
 and 
$\sigma_{f}=5.50$
 are the baseline and follow-up 4 standard deviations (SDs), respectively, and 
r=0.546
 is the within-person correlation. Substituting these values gives 
Var(Δ)≈30.0
, yielding 
${\mathrm{SD}}_{\Delta }\approx 5.48$
.

We account for clustering between MHCs using design effect,

DE=1+(m−1)ICC

Where m = 50 is the average cluster size and ICC is the intraclass correlation. Under this framework (two-sided significance level 5 and 80% power), the minimum detectable difference in difference (DiD) effect in PHQ-9 points is approximately 0.94, 1.08, and 1.43 for ICC = 0.01, 0.02, and 0.05, respectively.

We will invite a subsample from the quantitative cohort of patients to interviews through a purposive sampling strategy (23). Patients will be selected with varying treatment exposure (≥1 session) to capture diverse treatment experiences and outcomes. The qualitative sample size will be guided by content saturation.

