Perceptions and experiences of MHC model in the community	Focus groups	Community stakeholders

**Table 4 tab4:** Implementation key indicators, data sources, and target group.

Key indicators	Data source	Target group (level)
% of services delivered as planned Consistence of referral over time per MHC	Center records	Providers Centers
organizational readiness	Organizational Readiness for Implementing Change (ORIC) (49)	Providers
Themes describing core implementation components of fidelity, facilitators, and barriers	Interviews	Directors
Themes capturing real world implementation in practice	Interviews	Providers
Quality and effectiveness of collaboration in implementation	Focus groups	Community stakeholders
Documentation and utilization of feedback and iterative learning from workshops	Workshops	Providers, MH4U team and community stakeholders

**Table 5 tab5:** Maintenance key indicators, data sources, and target group.

Key indicators	Data source	Target group (level)
Long-term patient mental health outcomes	PCL-5, PHQ-9, PHQ-15, GAD-7, AUDIT, EQ-5D EQ-VAS and SWEMWBS	Patients
Robustness of long-term effects across patient subgroups Long-term attrition and differential retention by patient characteristics or clinical condition	Center records	Patients
Center-level adaptations post-project Organizational-level sustainability	Interviews	Providers
	Focus groups	Community stakeholders
Engagement in planning and implementing long-term sustainability of MHC practices	Workshops	Providers, MH4U team and community stakeholders

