##### Patient

Eligible patients for the cohort will receive a flyer during their regular visit at the MHC, containing essential study information with a QR code directing them to a Research Electronic Data Capture (REDCap) registration form (26, 27). We will assess the eligibility based on the submitted registration data. Eligible participants will then be contacted via their preferred way of communication and provided with a personalized link to provide informed consent and complete the self-administered quantitative assessment instruments. Follow-up assessments will be conducted via REDCap at three- and six-month intervals after baseline.

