##### Provider

All providers affiliated with the participating MHCs and MHCs that are not supported by MH4U will be invited to participate through a study summary along with a personalized Redcap link, through which they can provide informed consent and complete the quantitative assessment instruments. All providers will be invited again to complete the same set of instruments at the follow-up, which will be approximately one year from the baseline.

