##### Patients

Longitudinal patient outcome data and demographics questionnaires will be analysed and compared to data from the MAP studies. MAP cohort differs at baseline from patients receiving MHCs care. Consequently, we will use inverse probability weighting (IPW) to improve comparability. The IPW model will include key covariates (e.g., age, sex, baseline symptom severity, and prior mental health service use), creating a pseudo-population in which these covariates are balanced between groups. Weighted analyses will be used for all primary MAP vs. MHC outcome comparisons. Additionally, sensitivity analyses will be carried, restricting the sample of MAP subjects to those seeking care and/or with a comparable baseline outcome levels.

We will conduct these analyses on 2 primary cohorts:

1 Retained in care cohort (per protocol style):

This cohort includes patients who remained engaged in MHC care and completed baseline, follow up 1 and 2.

2 Care initiators cohort (intention to treat style):

This cohort will include all enrolled participants regardless of adherence or continued engagement.

For both cohorts, we will estimate intervention effects using DiD approach, comparing pre–post changes in outcomes between MHCs and the MAP cohort, depending on outcome availability and harmonization. Regression models will include center fixed effects and time fixed effects, with the DiD estimand given by the treatment-by-post (or treatment-by-time) interaction. Where multiple follow-ups are available, we will implement an event-study specification (baseline, follow-up 1, follow-up 2). We will obtain 95% confidence intervals, and *p*-values via center-level wild cluster bootstrap (1,000 draws). As a robustness check for small-sample inference, we will also report results using a Kenward–Roger/Satterthwaite-style degrees-of-freedom adjustment. For retained in care cohort, we will adjust the analyses using inverse probability of censoring weighting (IPCW) to address differential loss to follow up.

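### The primary outcome and sample size are set at a one-year follow-up 4 that the stated patient schedule, retained cohort and event-study model do not contain

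*Protocol article*

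**What the plan says.** All places are in the protocol article.

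- **Sample size calculation:** the primary outcome is PHQ-9 change "from baseline to follow up 4 (approximately one year"). The variance is built from SDs of 5.97 and 5.50, which "are the baseline and follow-up 4 standard deviations (SDs), respectively, and" a within-person correlation of 0.546.
- **Abstract, Methods and analysis:** patient questionnaires go to a "prospective longitudinal cohort at baseline, three, and six months".
- **Quantitative data collection, Patient:** "Follow-up assessments will be conducted via REDCap at three- and six-month intervals after baseline".
- **Data analysis, Patients:** the retained-in-care cohort is made up of patients who stayed in care and "completed baseline, follow up 1 and 2". Where there are several follow-ups, "we will implement an event-study specification (baseline, follow-up 1, follow-up 2").
- **RE-AIM operationalization, Maintenance, and Table 5:** a future phase, at least six months after the second study phase, covers "Long-term patient mental health outcomes", with PHQ-9 among the instruments.
- **Quantitative data collection, Provider:** the only other one-year assessment stated is the provider follow-up, "which will be approximately one year from the baseline".

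**The concern.** The time point that defines the primary outcome and supplies every sizing input appears neither in the patient schedule nor among the named analysis time points. The abstract, the patient data collection section, the cohort definition and the event-study specification agree with one another, and all stop short of it.

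Two things are at stake. The first is pre-specification. The article does not say which contrast is the primary result: a three-month effect, a six-month effect, a pooled post effect or a one-year effect. That matters more than usual here, because the comparison is non-randomised, uses an external control cohort, and has its results shared with stakeholders at each phase. The second is the sample size statement. It describes what can be detected over about one year, while the analysis described runs to follow-up 2.

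**Working it through.** **Step 1. Set the time points side by side.**

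| Place in the article | Patient time points named |
|---|---|
| Sample size calculation (primary outcome, SD, correlation) | baseline, follow-up 4 (about one year) |
| Abstract | baseline, 3 months, 6 months |
| Quantitative data collection, Patient | 3 and 6 months after baseline |
| Retained-in-care cohort | baseline, follow-ups 1 and 2 |
| Event-study specification | baseline, follow-ups 1 and 2 |
| Care-initiators cohort | all enrolled, no visit named |
| Maintenance phase | at least six months after the second phase; no time from patient baseline |

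Reading follow-ups 1 and 2 as the three- and six-month visits is the natural mapping, although the article does not spell it out. Follow-up 3 is not mentioned anywhere in the visible text. Follow-up 4 appears only in the sample size section.

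**Step 2. Reproduce the plan's own figures.** Inputs from the Sample size calculation section: SDs 5.97 and 5.50, r = 0.546, 400 patients, cluster size 50, two-sided 5%, 80% power.

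- Var(change) = 5.97² + 5.50² - 2 × 0.546 × 5.97 × 5.50 = 65.89 - 35.86 = 30.04 (unrounded 30.035), so SD = 5.48.
- Design effect = 1 + 49 × ICC = 1.49, 1.98 and 3.45 for ICC 0.01, 0.02 and 0.05.
- Detectable effect = (1.960 + 0.842) × 5.48 × √(design effect / 400) = 0.937, 1.080 and 1.426.

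These match the stated 0.94, 1.08 and 1.43. The published figures therefore rest entirely on follow-up 4 inputs. (They match in a form with no variance for the control cohort; that is a separate matter and not part of this point.)

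**Step 3. Ask what they would be at six months.** The article gives no six-month SD or correlation, so this cannot be computed. For illustration only, hold both SDs and vary r. The range 0.45 to 0.70 is an assumption with no source in the article.

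- r = 0.45: Var = 65.89 - 0.90 × 32.835 = 36.34; √(36.34 / 30.04) = 1.10, so the detectable effect is about 10% larger.
- r = 0.70: Var = 65.89 - 1.40 × 32.835 = 19.92; √(19.92 / 30.04) = 0.81, so it is about 19% smaller.

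**The case against.** The strongest reply is that the one-year assessment is planned, under another name. The Maintenance phase is a patient-level phase, Table 5 lists PHQ-9 and long-term attrition within it, and the LHS operationalization section says RE-AIM indicators, including Effectiveness, will be compared between the first phases and the follow-up phase. If the second phase includes the six-month visit, which is an assumption, six further months gives about a year. The DiD estimand is also worded generically as a treatment-by-post or treatment-by-time interaction, and the care-initiators cohort carries no visit restriction, so a later wave could enter that model. Figure 1, the timeline, is not available and may show more.

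Much of this stands. A reader might infer that patients are assessed only at three and six months, that the primary endpoint will never be collected or analysed, or that the study cannot produce its primary result. The article does not support those readings, because it plans a later PHQ-9 assessment and has a model that could accommodate it.

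A reader might also infer from the range in Step 3 that the study is underpowered at six months. It does not show that. The range is unsourced, and if correlation falls as the interval lengthens, r at six months would exceed 0.546 and, with the SDs held, the stated detectable effects would be conservative.

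What the reply does not do is remove the mismatch. The Maintenance phase is timed from a study phase, has no upper limit, is not called follow-up 4 and belongs to a different RE-AIM dimension from the effectiveness comparison. Nothing links it to the primary contrast. Even if Figure 1 displays a later wave, the abstract, the patient schedule, the retained cohort and the event study would still disagree with the sample size section. Nor is this a detail left to a fuller document: the article states the schedule, cohort and model terms, and a separate analysis plan could not align them without contradicting this text.

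**Conclusion.** The point holds as an internal inconsistency over when the primary outcome is measured and analysed, and it must be fixed. Follow-up 4 is undefined for patients in the visible text, absent from the stated patient schedule, and not named in the retained cohort or the event study. The sizing is arithmetically correct but applies to a time point other than the one the analysis section describes.

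The effect on the detectable difference is unknown, because no six-month inputs are given; the +10% to -19% range is illustrative and the conclusion does not depend on it. The conclusion rests on the visible text, with Figure 1 unseen, and on follow-ups 1 and 2 being the three- and six-month visits.

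**What to change.** Name one primary time point and use it in the abstract, the patient schedule, the cohort definitions, the DiD or event-study term and the sample size. Either option works:

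- **(a) Follow-up 2 (six months) as primary.** Restate the primary outcome accordingly, and recompute the SD, correlation and minimum detectable effects from data for that interval. Leave the one-year value to Maintenance.
- **(b) One year as primary.** State which wave is follow-up 4 (for example, the Maintenance wave), date it from each patient's baseline with a window, add it to the patient schedule and the retained-cohort definition, and name its interaction term as the primary contrast. The present sizing inputs then refer to the right interval.

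Under either option, define the visit numbering once and say which of the remaining time points are secondary.

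The cost is wording for (b) if the Maintenance wave is follow-up 4, wording plus a recalculation for (a), and at most one additional online questionnaire round if one year is kept and no existing wave falls at that time.

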##### The external control cohort

The external control data will be drawn from the Mental Health Assessment of the Ukrainian Population (MAP) studies, a large-scale cohort designed to better understand the mental stress experienced by the Ukrainian population as a result of the war (24, 25). MAP participants include adults aged ≥18 years across multiple oblasts in Ukraine. They were recruited using probability-based sampling to ensure representativeness of the general population.

#### Providers

All providers will be recruited, given the limited and well-defined staff composition at each MHC, for both the quantitative and qualitative components.

Given the ongoing war, we will recruit a control group of providers to enhance quantitative data interpretability. This control group will include all providers from eight MHCs that are not supported by MH4U.

